# HANDLING OF MISSING VALUES AND OTHER DATA CONVENTIONS

Missing values will be handled by listwise deletion in all analyses.

# STATISTICAL METHODOLOGY

## General principles

### Multiplicity

In accordance with study objectives, several comparisons will be made. To test the primary endpoint one risk ratio will be tested for significant difference from 1. To test the secondary endpoints, one comparison will be made for the endpoint concerning the effect of surgical technique on rectua abdominis muscle atrophy (mesh vs cruciate or circular incision) and one comparison will be made for the endpoint concerning the effect of stoma location on the parastomal hernia rate. We are aware of the risk for a type 2 error, but have chosen to perform the analyses with this knowledge and will interpret results with causion.

### Interpretation of results

Due to randomization of surgical technique in the data material, any estimated effects of surgical technique on risk of rectus abdominis muscle atrophy can be interpreted causally.

Estimated effects of rectus abdominis muscle atrophy on risk of parastomal hernia and of stoma location on risk of rectus abdominis muscle atrophy cannot be interpreted causally. Instead, any such effects should be interpreted as correlational.

### Type of analyses

The primary analyses for all endpoints will be adjusted analyses. Existence of serious multicollinearity as well as potential interaction effects between the explanatory variable and/or the covariates will be explored.

## Sample size

The StomaConst study based its sample size on a power computation using a two-sided proportion test using normal approximation of the binomial distribution to obtain 80% power for a significance level of 0.05 and a true difference in proportion of 20%. This gave a sample size of 62 per group (three groups, one for each surgical technique).

For the present study, only patients for whom a one-year CT examination was performed at one of the Swedish centers are included, giving a sample size of 140. Approximating the incidence of rectus abdominis muscle atrophy as 37% for the mesh arm and 2% for the cruciate/circular arm (following Täckström 2022)[[2](#_ENREF_2)], 21 subjects are expected to display rectus abdominis muscle atrophy. Using the same test and significance level as above and assuming 44% incidence of parastomal hernia in the group without rectus abdominis muscle atrophy (following Correa Marinez 2020)[[1](#_ENREF_1)], this allows detection of a difference in proportion of 30% with 80% power for the primary endpoint.

For the secondary endpoint investigating risk ratio of surgical techniques for developing rectus abdominis muscle atrophy, the surgical technique arms consist of 88 subjects (cruciate/circular) and 52 subjects (mesh) respectively. Assuming rectus abdominis muscle atrophy incidence per arm as above, this gives >99.9% power.

Power for the secondary endpoint investigating risk ratio of stoma position for developing parastomal hernia is not easily computable in advance without knowledge of the distribution of stoma position in the sample. Thus, this power computation will be performed post-hoc.

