# INTRODUCTION

This Statistical Analysis Plan (SAP) details the statistical and data related aspect of a planned manuscript on assessing whether rectus abominis muscle atrophy (*defined as a thinner muscle on the stoma side as seen on a postoperative computer tomography (CT) scan*) constitutes a protective factor for parastomal hernia (*defined as any herniation of intraabdominal content beyond the abdominal wall or a hernia sac identified in the prone or supine position on CT scan (if only the latter was available)*) as well as whether surgical technique used in colostomy construction constitutes a risk factor for rectus abdominis muscle atrophy and whether stoma placement (*measured from the medial limit of the muscle on 1-year CT scan)* constitutes a risk factor for parastomal hernia.

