# ANALYSIS OBJECTIVES

The primary objective is to investigate if rectus abdominis muscle atrophy is a risk factor for development of parastomal hernia one year after surgery.

Secondary objectives are:

1. Are any of the investigated operative techniques risk factors for developing rectus abdominis muscle atrophy?
2. Is stoma placement measured from the medial limit of the rectus abdominis muscle a risk factor for developing parastomal hernia?

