## Primary endpoint

The primary endpoint will be investigated using modified Poisson regression models using a sandwich estimator to compute confidence intervals and p-values, following Zou (2004), with parastomal hernia at one year as the response and MRA as a covariate. Other covariates to be adjusted for are stated in the “Covariates” section of the SAP. If clear overdispersion is detected in response data, it will instead be modelled using a negative binomial model.

The surgical technique variable will be included as a covariate in the model, as it is a potential confounder.

The result will be presented as a risk ratio for parastomal hernia at one year between MRA yes/no groups with 95% confidence interval and p-value for testing the null hypothesis of no difference in risk.

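### The 80% power stated for the primary endpoint belongs to an unadjusted two-proportion test; the planned adjusted risk-ratio model has about 50% (decrease) to 65% (increase) for the same 30-point difference

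*SAP*

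**What the plan says.** The Sample size section first describes the parent trial's calculation, a "two-sided proportion test using normal approximation of the binomial distribution to obtain 80% power for a significance level of 0.05". For the present study it takes the Swedish patients with a one-year CT, "giving a sample size of 140", and atrophy rates of "37% for the mesh arm and 2% for the cruciate/circular arm", which give 21 expected cases. It assumes 44% parastomal hernia without atrophy. It then continues "Using the same test and significance level as above" and concludes that "this allows detection of a difference in proportion of 30% with 80% power for the primary endpoint". It states neither a direction for the 30 points nor the variance form of the test.

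The analysis is set elsewhere. The Primary objective and Primary endpoint sections specify modified Poisson regression with a sandwich estimator, and Type of analyses makes the adjusted analysis primary for every endpoint. Seven covariates are listed, and on technique the plan says: "The surgical technique variable will be included as a covariate in the model, as it is a potential confounder".

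The direction is worded in two ways. The Introduction asks whether atrophy "constitutes a protective factor for parastomal hernia"; the Analysis objectives ask whether it "is a risk factor for development of parastomal hernia one year after surgery".

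**The concern.** The 80% is attached to the primary endpoint, but the test behind it will not be run on that endpoint. Two differences matter. The planned test works on the log risk ratio, where few events in the small group are costly. The planned model also holds technique fixed, while the plan's own rates put nearly all atrophy cases in one technique arm.

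If the figure is carried into the manuscript, a null result will be read as having had 80% power to detect a 30-point difference. The planned test would in fact miss such a difference about a third to a half of the time. Because the SAP gives no direction and its two statements of purpose point opposite ways, the reader cannot tell which case the 80% describes.

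**Working it through.** **Inputs (SAP, Sample size).** N = 140, with 52 mesh and 88 cruciate/circular; atrophy 37% and 2%; hernia without atrophy 44%; two-sided alpha 0.05. Expected atrophy cases: 52 × 0.37 + 88 × 0.02 = 19.24 + 1.76 = 21, so the groups are 21 and 119. A 30-point difference means 14% or 74% hernia with atrophy.

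**Step 1: reproduce the stated figure.** With pooled variance, power = Φ[(0.30 − 1.96·SE₀)/SE₁], where SE₀ uses the pooled rate and SE₁ the separate rates.
- Decrease: pooled rate (21 × 0.14 + 119 × 0.44)/140 = 0.395; SE₀ = 0.1157; SE₁ = 0.0883; power = Φ(0.829) = 79.6%.
- Increase: pooled rate 0.485; SE₀ = 0.1183; SE₁ = 0.1060; power = Φ(0.643) = 74.0%.
- With unpooled variance, Φ(0.30/SE₁ − 1.96): 92% for the decrease and 81% for the increase.

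So the 80% is a correct figure for an unadjusted test.

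**Step 2: change only the test, to an unadjusted Wald test on the log risk ratio.** Variance = (1 − p₁)/(21·p₁) + (1 − 0.44)/(119 × 0.44).
- Decrease: 0.86/2.94 + 0.56/52.36 = 0.303; SE 0.551; |log(0.14/0.44)| = 1.145; power = Φ(1.145/0.551 − 1.96) = 55%. The 2.94 expected events supply almost all of the variance.
- Increase: 0.26/15.54 + 0.56/52.36 = 0.0274; SE 0.166; log(0.74/0.44) = 0.520; power 88%.

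**Step 3: add surgical technique.** The variance of atrophy explained by mesh is [52/140 × (0.37 − 0.15)² + 88/140 × (0.02 − 0.15)²]/(0.15 × 0.85) = 0.224. The large-sample sandwich variance H⁻¹MH⁻¹ was evaluated on the four cells mesh/atrophy 19.24, mesh/no atrophy 32.76, no mesh/atrophy 1.76 and no mesh/no atrophy 86.24. H has weights n·p and M has weights n·p(1 − p).
- Decrease: variance 0.325, which is 1.07 times the unadjusted value; power 52%.
- Increase: variance 0.0461, which is 1.68 times the unadjusted value; power 68%.

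**Step 4: simulate the planned model.** Several independent sets of runs used 2,500 to 6,000 trials per scenario, n = 140 and the ordinary (uncorrected) sandwich. Covariates were unrelated to atrophy and hernia, technique had no effect on hernia, and no data were missing. Rejection under the null was about 5–6%.

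| Model | 44% to 14% | 44% to 74% |
|---|---|---|
| Unadjusted modified Poisson | 54% (59%) | 82–84% |
| With technique | 46–50% (51–55%) | 67–70% |
| With technique and seven covariates | 48–52% (53–56%) | 64–67% |

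Figures in brackets count samples with no hernia among atrophy cases, about 5% of trials, as rejections. The unadjusted row takes atrophy as random at the plan's rates; the other rows also include runs with it fixed at 19 mesh and 2 other cases. A small-sample-corrected (HC3) sandwich gives less for the adjusted models: 37–42% for a decrease and 56–67% for an increase.

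**Step 5: what would give 80%?** For an increase, the full model reaches 80% at about 44% to 80%, or 36 points. For a decrease there is no usable threshold. At 44% to 6.5%, the chance of no event in 21 patients is 0.935²¹ = 24%, and about a quarter of simulated trials had no hernia among atrophy cases and hence no finite risk ratio. Power there is 79% if those trials count as rejections and about 53% if they do not.

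**The case against.** The strongest reply is that nothing was miscalculated. The SAP names its test, the 21 cases and the 80% both reproduce, and using a simple test to approximate a regression model is common. The 140 patients are existing data, so no enrolment decision depends on the figure. The Multiplicity section acknowledges type 2 error, and the primary result will carry a 95% confidence interval that shows what a null finding excludes. All of this is true, and it makes the point a mismatch between power calculation and model, not an arithmetic error. It does not make the specific 80% true of the planned test, and a general caution does not correct a specific number.

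Four stronger readings are tempting, and the documents do not support them:

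- **That the 80% holds in one direction only.** This depends on pooled variance, which the SAP does not state. The parent trial's 62 per group fits the pooled form at 30% versus 10%, but those rates are an assumption. With unpooled variance both directions exceed 80%.
- **That technique adjustment explains the shortfall in both directions.** For a decrease, the unadjusted Wald test already has only 54–59%, and adding technique costs a few points more.
- **That a decrease of 37 or 38 points would restore 80%.** That is so only if trials without an estimable risk ratio count as rejections.
- **That the direction of the test is unsettled.** Multiplicity and Primary endpoint both test a risk ratio against no difference. The conflict is in how the aim is worded.

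**Conclusion.** The concern stands as a mismatch: the stated 80% is not the power of the planned primary analysis. For 30 points, that analysis has about 50% power for a decrease (about 54% with zero-event samples counted as rejections) and about 65% for an increase.

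The causes differ by direction. For a decrease it is mainly the log-risk-ratio Wald test with about 3 expected events in 21 patients. For an increase it is mainly adjustment for technique, with a small further loss from the other covariates.

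The figures take the plan's rates as given and rest on three simulation assumptions: covariates unrelated to atrophy or hernia, no technique effect on hernia, and no patients lost to listwise deletion. Covariates correlated with atrophy, as the SAP's own graph draws several of them, or missing data would tend to lower power further.

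**What to change.** In Sample size, say that the 80% for 30 points refers to an unadjusted two-proportion test, and state its variance form and direction. Add that under the planned adjusted modified Poisson model a 30-point difference has about 50% power for a decrease and about 65% for an increase. Name both causes and list the simulation assumptions. For an increase, state that 80% needs about 36 points. Give no 80% threshold for a decrease, because the risk ratio is too often inestimable there.

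Word the aim identically in the Introduction and Analysis objectives, as the two-sided association that Multiplicity and Primary endpoint already test. In reporting, do not describe a null result as having had 80% power to exclude a 30-point effect; let the confidence interval show what is excluded.

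The cost is a short change of SAP wording and a less favourable stated power. The patients, the model and the estimate stay as they are.

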## Demography and patient characteristics

*<Example:*

- *Age (median (Q1 ; Q3))*
- *BMI (median (Q1 ; Q3))*
- *Gender (frequency(%))*
- *tumour stage (frequency(%)) >*

Pending dataset

## Primary endpoint

The primary endpoint will be investigated using modified Poisson regression models using a sandwich estimator to compute confidence intervals and p-values, following Zou (2004), with parastomal hernia at one year as the response and MRA as a covariate. Other covariates to be adjusted for are stated in the “Covariates” section of the SAP. If clear overdispersion is detected in response data, it will instead be modelled using a negative binomial model.

The surgical technique variable will be included as a covariate in the model, as it is a potential confounder.

The result will be presented as a risk ratio for parastomal hernia at one year between MRA yes/no groups with 95% confidence interval and p-value for testing the null hypothesis of no difference in risk.

## Secondary endpoints

The secondary endpoints will be investigated using modified Poisson regression models using a sandwich estimator to compute confidence intervals and p-values[[3](#_ENREF_3)]. For the secondary endpoints concerning surgical techniques, MRA at one year will be included as the response and surgical technique as covariates. For the secondary endpoint concerning stoma placement, parastomal hernia at one year will be included as the response and stoma placement will be included as a covariate. Other covariates to be adjusted for are stated in the “Covariates” section of the SAP. If clear overdispersion is detected in response data, it will instead be modelled using a negative binomial model.

For the secondary endpoint concerning stoma placement, the surgical technique variable will be included as a covariate in the model, as it is a potential confounder.

The results for the endpoints concerning surgical technique will be presented as risk ratios for MRA between surgical technique groups with 95% confidence intervals and p-values for testing the null hypotheses of no difference in risk.

The results for the endpoints concerning stoma placement will be presented as risk ratios for parastomal hernia at one year for a unit difference in stoma placement with 95% confidence interval and p-value for testing the null hypothesis of no difference in risk.

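### If no control patient has atrophy (17% chance at the plan's own rates), the planned model for the surgical-technique endpoint returns an arbitrary risk ratio with a falsely narrow interval, and no fallback is specified

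*SAP*

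**What the plan says.** The Secondary endpoints section analyses this question with modified Poisson regression and a sandwich estimator. It states that "MRA at one year will be included as the response and surgical technique as covariates", adjusts for the listed covariates, and reports "risk ratios for MRA between surgical technique groups with 95% confidence intervals and p-values". The only alternative model is negative binomial, used if overdispersion is seen. Additional analyses lists none, and Type of analyses makes the adjusted analysis primary for every endpoint.

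The Sample size section supplies the figures: "Approximating the incidence of rectus abdominis muscle atrophy as 37% for the mesh arm and 2% for the cruciate/circular arm"; "the surgical technique arms consist of 88 subjects (cruciate/circular) and 52 subjects (mesh) respectively"; "21 subjects are expected to display rectus abdominis muscle atrophy". It gives power above 99.9% for this comparison, from a normal-approximation test of two proportions.

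The contrast is mesh against the two incision techniques pooled. Multiplicity counts one comparison, Sample size uses 88 against 52, and the causal diagram codes mesh or no mesh.

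**The concern.** A log-link model estimates the risk ratio from the event rate in each arm, so it needs at least one event in the reference arm. At a 2% rate in 88 patients an empty reference arm is a realistic outcome. The risk ratio then has no finite maximum likelihood estimate.

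The sandwich variance does not reveal this. It is built from squared residuals, which are close to zero in an arm with no events and a fitted mean near zero. The output therefore looks like a very precise result. The model-based standard error would be enormous and would show the problem, but the SAP does not use it.

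Interpretation of results singles out this endpoint as the one whose effect may be read causally. If the cell is empty, the analysts must either report a meaningless risk ratio or choose a method after seeing the data.

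**Working it through.** **Inputs (SAP, Sample size).** Control arm n = 88, rate 2%. Mesh arm n = 52, rate 37%. Total 140.

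**The plan's own figures reproduce.**
- Expected atrophies: 52 × 0.37 + 88 × 0.02 = 19.24 + 1.76 = 21.0, as stated.
- Power (two-sided 5%, pooled normal approximation, 2% of 88 against 37% of 52): 99.95%, consistent with the stated figure above 99.9%.

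**Chance of an empty control arm.** P(0) = (1 − p)^n.
- p = 2%, n = 88: 0.98^88 = 0.169.
- p = 1%: 0.99^88 = 0.413. p = 3%: 0.97^88 = 0.069. p = 5%: 0.95^88 = 0.011.
- The SAP deletes incomplete cases listwise. If that left 80 controls (an assumption), 0.98^80 = 0.199.

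**What the planned model returns for 0/88 against 19/52** (19 is the rounded mesh expectation; crude model, technique only).
- R, the SAP's software, at default settings: convergence reported, log RR 20.3, sandwich SE 0.183 (HC1 0.184, HC3 0.186), z = 111, 95% CI for the risk ratio about 4.6e8 to 9.3e8. Model-based SE: 2732.
- Python: log RR 23.7, sandwich SE 0.183, CI about 1.3e10 to 2.8e10.
- The two programs differ by a factor of about exp(23.7 − 20.3) = 30 on the same data. The value reflects where iteration stops, not the data.
- With seven simulated covariates added (200 fits), the medians were log RR about 23.6 and SE about 0.19.

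**Why the SE is small.** The mesh arm contributes (33/52)/19 = 0.0334 to the variance, and √0.0334 = 0.183. By algebra the empty arm contributes 88μ²/(88μ)² = 1/88 = 0.0114 whatever its fitted mean μ, which would give √0.0448 = 0.212. In double precision that term is lost at the converged μ, so programs print 0.183. The interval is falsely narrow on either figure.

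**With at least one control event** (probability 1 − 0.169 = 0.831) the crude model is finite. The 95% CI is about 4.4 to 233 with one event and 3.9 to 66 with two. In simulations of the adjusted model with seven simulated covariates, coverage of the nominal 95% interval was 95% to 96% in this case and 0% when controls had no event. Overall coverage was 80%, which is 0.83 × 0.96.

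**The negative binomial switch.** It keeps the log link and diverges in the same way. A 0/1 outcome with mean p also has variance p(1 − p), below the Poisson variance p, so overdispersion would not trigger it.

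**Simple methods on the same tables.**
- 19/52 against 0/88: risk difference 36.5 points (Newcombe 24.1 to 50.1); score lower limit for the risk ratio about 8.6, with no finite upper limit; Fisher p = 5.6e-10.
- 19/52 against 2/88: risk difference 34.3 points (21.2 to 48.0); score interval for the risk ratio 4.4 to 60.8; Fisher p = 6.4e-8.

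**Firth penalisation with the sandwich.** For 0/88 against 19/52 the penalised risk ratio is (19.5/52)/(0.5/88) = 66. Its sandwich SE of 0.21 gives 44 to 99; the model-based interval is about 4 to 1,093. Penalising the estimate without changing the interval leaves the false precision in place.

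**The case against.** The case against is substantial, and much of it stands.

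- **The failure is conditional and the endpoint is secondary.** In about 83% of cases at the assumed rate, the model gives a finite estimate with near-nominal coverage. The 80% overall coverage is the empty-cell event counted again, not a second fault.
- **The conclusion about a difference is safe.** The planned Wald test and Fisher's test both reject in the same direction. A risk ratio in the hundreds of millions would probably be noticed, and the planned Table 2 shows the counts. But the declared endpoint is the risk ratio, and the plan does not say what would replace it.
- **The 17% depends on one approximated rate** from a cited study not available here. The range of 1.1% to 41% belongs with it.

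A reader might infer three stronger points that the document does not support.

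- The objective "Are any of the investigated operative techniques risk factors for developing rectus abdominis muscle atrophy" and the plural wording in Secondary endpoints could suggest separate contrasts with a single incision arm, where empty cells would be likelier. Multiplicity and Sample size plan and size one pooled contrast, and the SAP gives no split of the 88.
- About 2.6 events per slope (21 events, 8 slopes) might suggest that the model breaks down generally. The simulations do not show this once a control event exists.
- The chance of zero or one control event, about 47%, might be read as the failure rate. One event gives a wide interval, not a breakdown.

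**Conclusion.** The point holds as a conditional failure. At the SAP's 2% rate and 88 controls there is about a one-in-six chance that the planned analysis of surgical technique on atrophy gives an arbitrary risk ratio with a falsely narrow interval, and the plan names no method that would rescue it. The probability rests on the assumed rate and on the number of complete controls. The behaviour of the model in an empty cell does not depend on either.

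It does not follow that the comparison lacks power, that its test is unreliable, or that the model is unsuitable when control events occur. Severity: should-fix.

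**What to change.** In Secondary endpoints, keep the adjusted modified Poisson model and add:

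1. Always report beside it the unadjusted mesh against pooled cruciate/circular contrast: risk difference with a Newcombe or score 95% CI, an exact p-value, and a risk ratio with a score interval.
2. If the control arm has no atrophy, these results replace the modified Poisson risk ratio. The score interval is then one-sided (lower limit about 8.6 for 19/52 against 0/88).
3. Any Firth-penalised adjusted risk ratio uses profile penalised-likelihood intervals, not the sandwich.

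The cost is a few lines of SAP text and R code. The downside is an unadjusted estimate if the fallback is triggered. Randomisation supports that estimate only in part, because the analysis set is per protocol and limited to Swedish patients with a one-year CT. That is a reason to keep the adjusted model as primary when it can be estimated.

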## Type of analysis

The patients will be analyzed per protocol.

VARIABLES AND ENDPOINTS
Primary objective

The primary endpoint is the risk ratio between groups with and without rectus abdominis muscle atrophy for having parastomal hernia one year after surgery. The primary endpoint is derived from a modified Poisson regression model controlling for several covariates.

The variables associated with the primary objective are presence of rectus abdominis muscle atrophy <*varname_RAMatr>* and parastomal hernia at one year <*varname_Parastomal hernia>*.

Presence of rectus abdominis muscle atrophy will be determined by simultaneous retrospective examination by two radiologists of one-year CT examinations. Both assessors will examine the same image material, note their own judgment (rectus abdominis muscle atrophy yes/no) and then reach a consensus judgment. Cohen’s kappa will be reported as a measure of inter-rater agreement.

The determination of parastomal hernia at one year performed in the Stoma-Const trial will also be used in this study.

Further details are given in Table 1.

Secondary objectives

The secondary endpoints are the risk ratios between surgical techniques for developing RAM atrophy, and the risk ratio of a difference of stoma placement in RAM, measured from its medial limit, for developing parastomal hernia, respectively. The secondary endpoints are derived from modified Poisson regression models controlling for several covariates.

For the surgical techniques endpoint, the alternative technique of reinforcement of abdominal wall with a mesh around the stoma will be compared to the control techniques of cruciate incision and circular incision.

The variables associated with the secondary objectives are surgical technique <*varname_surgtec>* and presence of RAM atrophy <*varname_RAMatr>*, and stoma placement in RAM <*varname_stomaloc>* and parastomal hernia at one year <*varname_* parastomal hernia*>*, respectively.

Stoma placement in RAM will be determined by one radiologist assessor, measuring the distance from the medial RAM limit to the medial stoma border in mm.

Further details are given in Table 1.

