2. BMI
3. Sex
4. Method of surgery (laparoscopic/open surgery)
5. Comorbidity as defined in the Stoma-Const trial including diabetes and cardiovascular disease. Defined as yes or no to one of several co-morbidity questions (question 15 in preoperative questionnaire)
6. Stoma aperture area (from the perioperative CRF question 16, fascia incision diameter
7. Stoma placement in the rectus abdominis muscle (where it is not the endpoint variable) measured by one radiologist as the distance from the midline to the beginning (medial) of the stoma aperture

These covariates will be investigated for potential multicollinearity before modelling. If serious multicollinearity is detected, some variables may be excluded.

Further details are given in Table 1.

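### Stoma placement is tested as one log-linear slope with no check of its shape; a labelled linearity check would be a cheap improvement

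*SAP*

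**What the plan says.** The SAP's Analysis objectives ask: "Is stoma placement measured from the medial limit of the rectus abdominis muscle a risk factor for developing parastomal hernia". Under Variables and endpoints (Secondary objectives), one radiologist determines placement by "measuring the distance from the medial RAM limit to the medial stoma border in mm". The Secondary endpoints section fits a modified Poisson model in which "stoma placement will be included as a covariate", and presents "risk ratios for parastomal hernia at one year for a unit difference in stoma placement with 95% confidence interval" with a p-value. The Multiplicity section states that "one comparison will be made for the endpoint concerning the effect of stoma location on the parastomal hernia rate".

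The only model exploration is in Type of analyses: "Existence of serious multicollinearity as well as potential interaction effects between the explanatory variable and/or the covariates will be explored". The Additional analyses section lists none. No quadratic term, spline, categories or linearity check for placement appears anywhere. Planned Table 2 sets stoma position against surgical technique, not against hernia, so it would not show the shape either.

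The covariate list describes placement with a different origin: "the distance from the midline to the beginning (medial) of the stoma aperture".

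**The concern.** Placement is the exposure of its own objective, so the form in which it enters the model decides the answer. One coefficient on a log link assumes that each further millimetre multiplies hernia risk by the same factor across the whole range. If risk were instead higher at both ends of the observed positions than in the middle, the rises would offset each other in the slope. The estimate could then lie near 1 despite a real relation. If risk rose at one end only, the slope would pick up some of it, but the reported ratio would describe a steady trend that is not there. As written, the plan has no step that would reveal either case.

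**Working it through.** **No figure to reproduce.** The Sample size section gives no power for this endpoint. It defers the calculation to a post-hoc one because the distribution of placement is not known.

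**Inputs from the SAP.** 140 patients ("giving a sample size of 140"), 52 of them mesh; 44% hernia (the SAP's assumption for patients without atrophy, used here as the overall rate); two-sided 0.05, as in the parent trial's calculation.

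**Assumptions not in the SAP.** The distribution of placement and the shape of the risk.

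**Model.** log Pr(hernia) = b0 + b1·x + covariates, where x is distance. The risk ratio for a difference of d mm is exp(b1·d), whatever the starting point. If x is symmetric about its mean and risk is an even function of the distance from that mean, x and risk are uncorrelated and the fitted slope is about zero.

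**Simulation 1.** Placement normal, 8 covariate terms (technique plus the listed covariates) plus placement, mostly 2,500 to 4,000 trials per scenario. Risk is raised beyond 1 SD on either side of the centre, which covers 32% of patients when centred on the mean. The implied risks are:

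- Ratio 2: 0.44/(0.68 + 0.32 × 2) = 0.44/1.32 = 33% in the middle, 67% outside.
- Ratio 1.7: 0.44/(0.68 + 0.32 × 1.7) = 0.44/1.224 = 36% and 61%.

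Share of trials with p < 0.05 (ranges are across repeats):

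| Assumed truth | Planned slope test | Added quadratic term, HC3 |
|---|---|---|
| No effect | 6.0-6.7% | 4.0-4.4% |
| Ratio 1.7, both sides, centred on the mean | 5.4-6.3% | 42-43% |
| Ratio 2, both sides, centred on the mean | 5-6% | 61-62% |
| Ratio 2, low-risk zone shifted 0.5 SD | 36-39% | 33% |
| Ratio 2, low-risk zone shifted 1 SD | 64% | 6% |
| Ratio 2, medial side only | 59% | 20% |
| Linear, 1.28 per SD | 75-76% | not applicable |

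With the ordinary sandwich (HC0), the quadratic term's false-positive rate is 6.8-8%, hence HC3.

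**Simulation 2.** No covariates, 3,000 trials per scenario, placement over an assumed 0-50 mm, u = (x − 25)/25, risk = 0.25 + 0.5u² (25% in the middle, 75% at the ends). The slope test is compared with a joint 2-df test of slope and quadratic term, with the ordinary sandwich:

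| Placement distribution | Slope | Joint test |
|---|---|---|
| Uniform | 4% | 93% |
| Symmetric, centre-weighted | 5% | 74% |
| Skewed medially | 24% | 73% |

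If the truth is linear (0.44 + 0.19u), replacing the slope by the joint test lowers power from 76% to 64%, 53% to 41% and 47% to 40% respectively. The joint test's false-positive rate is 5-7%. This argues for adding a check, not for replacing the planned test.

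**A two-test rule.** If slope and curvature together decided whether placement is called associated, at least one would be significant in about 10-12% of null trials, against about 6% for the slope alone.

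**The case against.** The objective is itself anchored on the medial limit, and a ratio per unit of that distance is a natural answer to it. The SAP nowhere proposes that both very medial and very lateral stomas carry more risk. The near-zero power in the centred scenarios comes from placing the curve exactly on the mean position. Move it, and the slope test recovers, at 1 SD even beating the quadratic term by 64% to 6%. Muscle width is not among the planned measurements, so a quadratic in mm cannot measure nearness to the lateral edge. All of this stands and limits the point.

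Three stronger readings are tempting, and the document supports none of them.

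- A reader might infer that placement would be reported as not a risk factor. No sentence says that a non-significant slope will be read that way; the Multiplicity section acknowledges type 2 error and promises cautious interpretation.
- A reader might infer that the test has no power against any edge effect. That holds only for a curve balanced around the observed positions, whose distribution the SAP says is unknown.
- A reader might take the causal graph's two routes from placement to hernia (direct and through atrophy) as evidence of curvature. Arrows say nothing about functional form, and two routes can add up to a monotone effect.

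That the unit is 1 mm is also an inference from the measurement. The results text does not name the unit, and the appendix table that might do so shows only a template name.

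**Conclusion.** The point holds as a cheap improvement to one secondary endpoint. The plan rests on log-linearity for the exposure of its own objective and never checks it. What that could cost ranges from nearly all the power, if a curve happens to be balanced around the observed positions, to part of it plus a possibly misleading summary if the curve is off-centre or one-sided. If the relation is linear on the log scale, nothing is lost. These figures rest on assumed distributions and on a large assumed effect (risk doubled). The primary objective's planned test is not at issue here.

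**What to change.** Keep the slope as the single planned comparison in the Multiplicity section. Add to the stoma-placement text under Secondary endpoints:

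> As a labelled check of linearity, a quadratic term (or a 3-knot restricted cubic spline) for placement will be added, with HC3 sandwich variance, and fitted risk with its 95% confidence band will be plotted against distance. If there is evidence of curvature, the single risk ratio will not be presented as a sufficient summary of the association.

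Do not add a rule that calls placement not associated when both tests are non-significant. It would let two unadjusted tests decide one question and would read non-significance as absence of an association, although curvature is missed in about 39-57% of the centred scenarios above (100 − 61 and 100 − 43).

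The two descriptions of placement (from the medial muscle limit and from the midline) should be reconciled at the same time, so that the check and the plot use one defined distance. Reporting the ratio per 10 mm is an optional matter of presentation.

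Cost: two sentences, one further exploratory model and one plot, with no new readings. The check has limited power (about 40-60% in the centred scenarios, less when the curve is off-centre). It tests curvature in the measured distance, not nearness to the lateral edge. The Demography section still marks the dataset as pending, so the check can be fixed in advance.
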